#### Safety Analysis

Adverse events (AEs) will be documented by medical OST staff. An AE is defined as any new untoward medical occurrence or worsening of a pre-existing medical condition in a clinical investigation subject administered study drug and that does not necessarily have a causal relationship with this treatment. An AE can therefore be any unfavorable and unintended sign (such as an abnormal laboratory finding), symptom, or disease temporally associated with the use of study drug, whether or not considered related to the study drug. The causal relationship to study drug is determined by a physician and should be used to assess all AEs.

A serious AE (e.g., life-threatening overdose) or possible other adverse drug reactions will be documented in the “Report on adverse drug reactions (ADRs)”. Analyses of safety outcomes will equally be conducted for both samples (PP and ITT).

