### Selection and Treatment of Participants

Inclusion and exclusion criteria are listed below. Patients who are not eligible for the treatment with injectable subcutaneous depot buprenorphine according to Summary of Product Characteristics (SmPC) will be excluded from the depot buprenorphine arm, but can be part of the control group, if pairwise matching criteria apply. If a patient drops out from treatment with injectable depot buprenorphine (and returns to previous medication or give up OST at all) he or she should be followed up for the whole study period (unless he/she withdraw the study consent).

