#### Primary Outcome Analysis

The main analysis will be carried out according to the intention-to-treat principle (ITT), considering all patients who have started the substitution treatment with injectable depot buprenorphine. The primary outcome measure is the difference of OSTQOL (20) scores between baseline (t_0_) and month 12 (t_4_) in the depot group. The average OSTQOL mean score will be compared between these time points and analyzed for statistical significance using dependent *t*-tests. It is tested against the statistical null hypothesis (H0) of a decrease or no change in the OSTQOL mean score. The alternative hypothesis (H1) consists in a significant improvement of the OSTQOL mean score, which corresponds to an improvement in quality of life of the patients.

H0: M (Month 12) ≤ M (baseline) (OSTQOL mean score at 12 months ≤ baseline OSTQOL mean score)H1: M (Month 12) > M (baseline) (OSTQOL mean score at 12 months > baseline OSTQOL mean score).

The hypothesis will be tested two-sided at a significance level of *p* < 5%. The statistical analyses will be made according to the intention-to-treat (ITT) as well as to the per-protocol (PP) principle. The PP sample is defined by all patients who have undergone OST with injectable subcutaneous depot buprenorphine for at least 12 months and for whom sufficient baseline and 12-month data are available. The ITT sample comprises all patients who provided a written consent, who have undergone the baseline assessment, and–for patients in the depot study arm–who have received the first dose of injectable depot buprenorphine. For the ITT analysis, data from all study patients will be used independently of their status in or out of treatment with injectable depot buprenorphine. Missing values at the 12-month time point will be replaced by missing imputation procedures. These may either include last observation carried forward (LOCF) approaches or longitudinal mixed model analyses using all available follow-up assessments. The choice of imputation procedures for the ITT analysis will depend on the proportion of missing values at the 12-month time point as well as the quantity of available data at 3-month and 6-month follow-up, and will be determined by sensitivity analyses.

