### Drop-Outs

Patients who cannot be analyzed (i.e., missing baseline and follow-up data, not starting treatment with injectable depot buprenorphine) will be excluded from the data analyses. If either the medication with injectable depot buprenorphine or OST treatment or study participation (or both) is discontinued, the reason for the termination or circumstance will be documented. Patients who change from the depot group to the control group or vice versa will be followed-up as long they withdraw their study participation or terminate OST (drop-out). In both cases the reasons will be documented. A drop-out analysis will be performed to determine potential drop-out criteria.

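### Safety is planned alike in PP and ITT: PP leaves out everyone who stops depot before 12 months, and ITT, if counted by original group, does not separate events on and off depot

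*Protocol article*

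**What the plan says.** The Safety Analysis section of the protocol article names two samples for safety and no other: "Analyses of safety outcomes will equally be conducted for both samples (PP and ITT".

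Both are defined under Primary Outcome Analysis:

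- **PP:** "The PP sample is defined by all patients who have undergone OST with injectable subcutaneous depot buprenorphine for at least 12 months". A further condition is that enough data exist at the start and at month 12.
- **ITT:** everyone with consent and a baseline visit; the depot arm must also have had a first injection. On patients who later leave depot, the rule is that "data from all study patients will be used independently of their status in or out of treatment with injectable depot buprenorphine".

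Follow-up continues through changes of medication. Under Selection and Treatment of Participants, a patient who leaves depot stays under observation: "he or she should be followed up for the whole study period". The Drop-Outs section covers both directions: "Patients who change from the depot group to the control group or vice versa will be followed-up".

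The AE definition is tied to exposure. It ends with a "disease temporally associated with the use of study drug, whether or not considered related to the study drug".

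**The concern.** Staying on depot for a year is itself an outcome that tolerability can affect. A safety table restricted to patients who managed it cannot show the events that made others stop. The article gives this table the same place as ITT and names no further safety sample.

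ITT restores the early stoppers but follows them off depot. If their later events are counted under depot, and events in controls who start depot are counted under treatment-as-usual (TAU), the by-group table answers a different question from how often AEs occur while patients are on depot. At stake is the description of depot tolerability in routine care. The primary endpoint is not affected.

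**Working it through.** **1. The plan's own figures (Sample Size Calculation).** Paired t-test, d = 0.25, two-sided alpha 5%, power 80%: n = 127.5, so 128. Drop-out: 128 / (1 − 0.40) = 213.3, stated as 213. Both reproduce. No figure is given for safety.

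**2. Who is in each safety sample.**

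| Patient | PP | ITT |
|---|---|---|
| Depot for 12 months, data sufficient | in | in, depot |
| Stopped depot early, for an AE or otherwise | out | in, depot, with later off-depot data |
| Control staying on TAU | out, read literally | in, control |
| Control who moves to depot | not addressed | in, control (if the original group is kept) |

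The PP column needs no assumption beyond the definition, except for the switched control, whom the text does not address. In the ITT column, the group under which AEs are counted after a switch is inferred from the general ITT rule; the article does not state it for AEs.

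**3. Size of the PP exclusion.** Assume the planned 40% means leaving depot or lacking month-12 data. Then 213 × 0.60 = 127.8 patients are in PP, and about 85 of 213 starters are out.

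**4. Off-depot time within the ITT depot arm.** Assume 40% stop at month m and everyone is followed for 12 months. The off-depot share of person-time is 0.40 × (12 − m)/12:

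- m = 1: 37%
- m = 3: 30%
- m = 6: 20%

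**5. Illustration on rates.** None of these AE rates is in the document. Assume 0.05 AEs per month on depot in completers, twice that in stoppers while on depot, 0.025 per month off depot, and 40% stopping at month 3.

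- On-depot events: 127.8 × 12 × 0.05 + 85.2 × 3 × 0.10 = 76.68 + 25.56 = 102.24
- On-depot person-months: 127.8 × 12 + 85.2 × 3 = 1,789.2, so the on-depot rate is 0.057
- PP rate: 0.050, or 0.875 of the on-depot rate. PP misses 25.56 / 102.24 = 25% of on-depot events (14% if stoppers have the completers' rate, 33% if three times it)
- ITT by group: (102.24 + 85.2 × 9 × 0.025) / (213 × 12) = 121.41 / 2,556 = 0.0475, or 0.83 of the on-depot rate

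Varying the stopping share over 20–40%, the stopping time over months 1–6 and the stoppers' rate ratio over 1–3, PP/on-depot runs from 1.00 down to 0.67. ITT/on-depot runs from 0.95 down to 0.80.

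**6. The direction is not fixed.** The ITT rate is a weighted average of the on-depot and off-depot rates. With 0.10 per month off depot in step 5, ITT becomes (102.24 + 76.68) / 2,556 = 0.070, which is above 0.057.

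For the percentage of patients with at least one AE, PP can also come out higher, because completers are exposed for longer. At constant hazard with the step 5 rates:

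- PP: 1 − exp(−0.6) = 45%
- Stoppers while on depot: 1 − exp(−0.3) = 26%
- All starters: 0.6 × 45% + 0.4 × 26% = 37%

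PP falls below the all-starter percentage only if the stoppers' rate ratio exceeds 12/m, that is 4 at month 3 or 2 at month 6.

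**The case against.** The ITT depot arm requires a first dose, so it is close to a conventional all-treated safety set, and no starter with a baseline assessment is lost from it. The AE definition refers to use of the study drug. The AE form records causal link to the substitution medication and time (Handling With AEs and ADRs), and that section promises that all AEs will be reported. Assigning events by medication is often left to an analysis plan. The word used for the two safety analyses may mean no more than likewise. Safety is not listed in Table 1.

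Much of this stands. A reader might infer that neither sample says anything useful about AEs on depot; that is too strong, since ITT gives AE incidence among depot starters. A reader might also infer that PP understates harm by construction. The exclusion is by construction, but the direction is not, as step 6 shows. Nor can a shortfall of a third to a half be claimed. For percentages, the ratio of PP to all starters is (1 − s)/0.6, where s is the share of patients with the AE who leave. It falls to 0.67 or 0.50 only at s = 60% or 70%, for which the document offers no support, and it is 1 at s = 40%. That the more favourable table would be the one quoted is speculation.

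The objection does not remove the stated choice of a 12-month completer sample for safety, which is fixed in the text rather than left open. Reporting every event does not supply a denominator or say how switchers are counted. The study-drug wording of the AE definition does not fit TAU controls, and the article does not use it to limit the ITT table to time on depot.

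**Conclusion.** The concern holds in a limited form. PP is badly chosen as a safety sample: by its definition it omits every early stopper and, read literally, every control. The omission is about 85 of 213 starters if the 40% drop-out is read as leaving depot or lacking month-12 data; the article does not say that it means this.

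ITT covers the starters but, as defined, does not separate time on depot from time off it, nor does it bring in controls who move to depot. This part rests on AEs being counted by original group, which is inferred.

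The size and direction of either bias depend on AE rates and stopping patterns that the document does not give. The figures in steps 4 to 6 are illustrations, not estimates. The change is worth making because it is cheap and safety reporting depends on it.

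**What to change.** Replace the sentence on safety samples along these lines:

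- **Main safety analysis:** all patients with at least one depot injection, including controls who switch, and all TAU patients with a baseline visit. Events and person-time are assigned to the OST medication in use at onset, with a separate category for time on no OST medication. Report counts and rates per person-time.
- **ITT:** keep as the table by original group, and say so explicitly.
- **PP:** drop for safety, or label it supplementary.

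The inputs are already planned: dates of ending OST or changing medication (Variables, under retention) and the time and causal link of each AE (Handling With AEs and ADRs). The sample size does not change.

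The cost is one derivation and one extra table. The by-medication rates will not be a comparison of the original matched groups and should be labelled accordingly, which is the reason to keep the ITT table beside them.

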### Sample Size Calculation

A study by Apelt et al. (30) showed a significant improvement in health-related quality of life (measured by SF-36) with an average effect size of *d* = 0.40 after 12 months among patients who switched from (levo-) methadone or buprenorphine to buprenorphine/naloxone. A study by Karow et al. (31) found effect sizes in the improvement of quality of life measured by MSQOL in patients treated with diamorphine between *d* = 0.73 (after 6 months) and *d* = 0.80 (after 12 months).

An α-error of 5% and a statistical power of 80% (β-error = 20%) will be used. In our study we anticipate a smaller effect size of d = 0.25 which will result in a minimum number of *N* = 128 patients. Further we estimate a drop-out rate of 40% until month 12 (t_4_) resulting in a sample size of *N* = 213 patients treated with injectable depot buprenorphine. Considering the same number of patients in the matched control group, the total sample size is *N* = 426. Under the conditions of an α-error of 5% and a statistical power of 80% this sample size allows for detection of statistically significant differences in group comparisons with an effect size of *d* = 0.35 or higher.

### Data Processing, Missing Data

The completion of the data sets is the responsibility of the OST physician and OST unit staff, who carry out the baseline and follow-up documentation and administer the patient questionnaires at the indicated study timepoints. Before study start, all OST physicians and OST unit staff will be trained in recruitment, study conditions, and data documentation. Within the study, all sheets documented by OST staff will be monitored for plausibility and completeness.

All data will be recorded continuously and checked for completeness, plausibility and correctness. For the evaluation of instruments and scales, the respective rules to handle missing data will be considered. Relevant missing clinical data will be requested by queries. Non-retrievable data become “missing data,” which can possibly be corrected in the context of the evaluation on the basis of substantive plausibility checks, so-called “self-evident corrections.”

Data entry and adjustments are carried out by study center (ZIS) staff who are not involved in the study coordination, monitoring or documentation. The statistical analyses will be done by using the statistics program SPSS 25 (32).

### Drop-Outs

Patients who cannot be analyzed (i.e., missing baseline and follow-up data, not starting treatment with injectable depot buprenorphine) will be excluded from the data analyses. If either the medication with injectable depot buprenorphine or OST treatment or study participation (or both) is discontinued, the reason for the termination or circumstance will be documented. Patients who change from the depot group to the control group or vice versa will be followed-up as long they withdraw their study participation or terminate OST (drop-out). In both cases the reasons will be documented. A drop-out analysis will be performed to determine potential drop-out criteria.

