### Assessment and Timelines

All data will be collected in case-report-forms (CRFs) including documentation sheets for clinical routine data and questionnaires for OST providers and patients. After baseline (t_0_), follow-up assessments will be made on month 1 (t_1_), month 3 (t_2_), month 6 (t_3_), and month 12 (t_4_). For the case that OST ends prematurely (before the end of the 12-month study period), study participation continues, and the patient will be asked to take part in the remaining follow-up assessments. All patients will receive reimbursements of € 10,-for each assessment.

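### The Drop-Outs section ends follow-up at OST termination for patients who change group, which contradicts the follow-up rule stated twice elsewhere; its exclusion sentence is also ambiguous against the ITT set

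*Protocol article*

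**What the plan says.** Follow-up after a change in treatment is described in three sections of the protocol article.

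- **Selection and Treatment of Participants.** A depot patient who goes back to an earlier medication "or give up OST at all) he or she should be followed up for the whole study period". The only exception is withdrawal of study consent.
- **Assessment and Timelines.** "For the case that OST ends prematurely (before the end of the 12-month study period), study participation continues", and the patient is asked to complete the remaining assessments.
- **Drop-Outs.** Patients who move from depot to control or "vice versa will be followed-up as long they withdraw their study participation or terminate OST (drop-out"). The wording is garbled, but the evident meaning is that follow-up runs until one of these two events.

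Two sections bear on who is analysed.

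- **Primary Outcome Analysis.** The ITT set requires consent, a baseline assessment and, in the depot arm, a first dose. No follow-up visit is required. For this analysis, "data from all study patients will be used independently of their status in or out of treatment with injectable depot buprenorphine", and missing month-12 values are imputed, either by LOCF or through a longitudinal mixed model.
- **Drop-Outs.** "Patients who cannot be analyzed (i.e., missing baseline and follow-up data, not starting treatment with injectable depot buprenorphine) will be excluded" from the analyses.

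**The concern.** The primary endpoint is an uncontrolled change in OSTQOL from baseline to month 12 within the depot group. What happens to depot patients who leave the medication, and then leave OST, therefore enters the result directly. If sites follow the Drop-Outs section, the month-12 questionnaire is not collected for those who changed medication first, and no later analysis plan can recover it. The ITT analysis would then rest on imputed values for patients whose observed values the rest of the protocol sets out to obtain.

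The exclusion sentence raises a separate question. If it is read broadly, patients who took depot, completed baseline and were never seen again are dropped, although the ITT definition keeps them and the imputation rule is there to deal with their missing month-12 values.

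**Working it through.** **1. The planned figures.** The inputs are in Sample Size Calculation ("An α-error of 5% and a statistical power of 80% (β-error = 20%) will be used"; "we anticipate a smaller effect size of d = 0.25"; 40% drop-out by month 12) and in Primary Outcome Analysis ("The hypothesis will be tested two-sided at a significance level of" 5%). A paired t-test with the noncentral t distribution gives n = 128, with power 0.8015. Allowing for drop-out, 128 / (1 − 0.40) = 213.3, against the stated 213. Both figures reproduce, and neither depends on the rules discussed here.

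**2. The follow-up rules applied to one patient.** Take a depot patient who returns to an earlier medication at month 3 and ends OST at month 8, without withdrawing consent.

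| Section | Month-12 OSTQOL |
|---|---|
| Selection and Treatment of Participants | collected |
| Assessment and Timelines | requested |
| Drop-Outs | not collected; follow-up ends at month 8 |
| Primary Outcome Analysis (ITT) | used if observed, imputed if not |

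The first section names exactly this kind of patient, so the Drop-Outs sentence cannot be set aside as a rule for a different group. The contradiction is direct.

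**3. How far it reaches.** The Drop-Outs sentence covers only patients who change group and then end OST. A patient who leaves OST straight from depot falls under the other two sections and stays in follow-up. The per-protocol set requires 12 months on depot, so the example patient is outside it in any case. For the primary endpoint the conflict therefore concerns the ITT analysis. Control patients who change group can affect the secondary group comparisons in the same way.

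**4. The exclusion sentence, read both ways.**

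- *Both baseline and follow-up missing:* these patients have no baseline assessment and are already outside the ITT set. There is no conflict.
- *Either one missing:* a treated patient with a baseline and no follow-up is in the ITT set under Primary Outcome Analysis and out under Drop-Outs. This is a conflict.

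Excluding depot patients who never start depot agrees with the first-dose criterion and is no error.

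The ambiguity has practical weight because Table 2 schedules no OSTQOL at month 1, so anyone lost before month 3 has a baseline score only. Under LOCF such a patient contributes a change of zero. Assume that the others change by 0.25 SD and that 10% or 20% are baseline-only (the documents give no share):

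- included: 0.90 × 0.25 = 0.225 SD, or 0.80 × 0.25 = 0.20 SD
- excluded: 0.25 SD

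**5. Range for a complete-data analysis.** Suppose retained patients change by 0.25 SD, and a share q is lost whose true mean change is m. Analysing the retained patients alone overstates the mean change by q × (0.25 − m). Both q and m are assumptions.

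| q | m = 0.25 | m = 0 | m = −0.25 |
|---|---|---|---|
| 10% | 0 | 0.025 | 0.05 |
| 20% | 0 | 0.05 | 0.10 |
| 40% | 0 | 0.10 | 0.20 |

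The 40% row is the protocol's whole expected drop-out, so it is an upper bound for this rule. If m exceeds 0.25 the sign reverses. The table shows what would happen without imputation. It does not estimate what remains after the planned imputation.

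**The case against.** The strongest reply is that the affected group is narrow, that the general rule is stated clearly in two sections while the conflicting sentence is visibly garbled, and that the protocol already has a safeguard. Crossovers who end OST are not removed from the ITT set by the follow-up rule. They lose later assessments only, OSTQOL is also scheduled at months 3 and 6, and month-12 values are imputed. All of this stands. It limits the consequence but does not remove the contradiction, and an imputed value is a poorer substitute for one that the protocol elsewhere plans to collect.

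A reader might infer more: that the rule turns the ITT analysis into one of patients who stayed, and so inflates the month-12 gain. With 10–20% lost and a 0.5 SD worse change among them, the formula gives 0.05–0.10 SD, which is 20–40% of 0.25. The documents do not support this. They give neither the share nor the deficit, and the arithmetic ignores the imputation. The direction is open too: the Introduction lists abstinence among treatment objectives and mentions depot use in preparing for regular termination, so ending OST is not always a poor outcome, although the same section says such terminations are rare.

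A reader might also infer that the exclusion sentence plainly contradicts the ITT definition. It does so only on the reading that either gap is enough.

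**Conclusion.** The conflict over follow-up is real and rests on the text alone: for patients who change group and then end OST, the Drop-Outs section cannot be reconciled with Selection and Treatment of Participants or with Assessment and Timelines, and it undercuts the ITT principle in Primary Outcome Analysis. The exclusion sentence is an ambiguity that needs settling, not a proven contradiction.

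Bias in the within-depot change is possible. It requires that the patients lost differ in their change from those retained and that the imputation does not correct for this. Under the assumptions shown, the complete-data overstatement runs from 0 to 0.20 SD against a planned 0.25 SD. That range is illustrative; the documents fix neither size nor direction. The sample sizes of 128 and 213 stand. The correction matters because uncollected month-12 data cannot be restored.

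**What to change.** Bring the Drop-Outs section into line with the other two: study assessments continue to month 12 for all patients, including those who change group and those who end OST, unless study consent is withdrawn. This concerns data collection only and leaves treatment decisions untouched.

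In the same section, state that the ITT set is the one defined in Primary Outcome Analysis. Only patients with no baseline assessment or, in the depot arm, no first dose are then excluded, and patients with a baseline but no follow-up stay in under the chosen missing-data method.

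The cost is a protocol clarification and a note to the OST units. The schedule in Assessment and Timelines already provides for the visits and their reimbursement, and no sample size changes.
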